##### RQ2: Characteristics of patients at PCBH centers compared to patients in standard care

Differences in sex, age, diagnostic pattern, comorbidities and prescribed medication will be investigated. Local registry data (age, sex), patient diagnoses F00-F99, Z56, and Z73F (ICD10, including specific diagnoses and combinations of diagnoses and comorbidities calculated using the Charlson Comorbidity Index) will be used. National registry data from the Swedish Prescribed Drug Registry (managed by the National Board of Health and Welfare) will be obtained concerning medication with psychotropic drugs coded as N05A, N05B, N05C and N06A according to the ATC classification system.

##### RQ3: Patient experiences with PCBH

Individual interviews (*n* = approximately 20) will capture aspects concerning patient satisfaction with the PCBH-based care, including the relationship with the behavior health consultant [32, 33]. A semistructured interview guide will be used. The interviews will be conducted on a continuous basis.

##### RQ4: Experience working with PCBH in terms of barriers to and facilitators of implementation

Individual interviews (*n* = approximately 20) with a mixture of health care professionals (physicians, nurses, and health therapists) will capture their experiences working with PCBH. A semi structured interview guide will be used, including questions on conceptualizations of PCBH and hinders at the centers for working with PCBH.

##### RQ5: Mental health therapists’ experience of their new PCBH-specific role as behavioral health consultants

Individual interviews (*n* = approximately 20) with mental health therapists (psychologists/psychotherapists) will aim to capture their experiences adopting their PCBH-specific role. A semi structured interview guide will be used. All interviews (RQ3-5) will be audio-recorded and transcribed verbatim.

##### RQ6: Work environment

Questionnaires will be administered to the staff at all PCBH centers regarding: sociodemography (age, gender, profession, year in that profession, how long the individual has worked at the primary care center), staff psychosocial factors (stress and well-being of employees measured by the Copenhagen Psychosocial Questionnaire (COPSOQ) III questionnaire), staff work commitment (measured by the Utrecht Work Engagement Scale), and exhaustion among coworkers (measured by the Karolinska exhaustion disorder scale [KEDS]). Registry data will also be used to assess sick leave among primary care staff.

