### Objectives

The project aim for this Pragmatic Stepped-Wedge Cluster Trial is to generate new knowledge concerning the impact of a real-world implementation of PCBH in routine primary care in Sweden. Twenty-four PCBH primary care centers will be compared with 48 standard care centers. The results will be investigated at the patient, staff and organization levels. Eight research questions (RQs) are addressed (for details, see Table 1):

**Table 1 Tab1:** Data sources and focus for each research question

Focus	Research question	Data source(s)
Patients	(RQ1) What are the effects of PCBH on patient outcomes compared to standard care?	• National registry data, INERA certification service (Swedish Social Insurance Agency): Patient sick leave due to mental health problems (i.e., sick leave due to ICD10: F00-F99, Z56, Z73F) • Local registry data: Referrals to secondary psychiatric care based on electronic medical records
	(RQ2) What characterizes patients who receive care according to the PCBH model compared to standard care?	Local registry data except where noted • Patient demography (gender, age) • Patient diagnoses F00-F99, Z56, Z73F according to ICD10, including specific diagnoses and combinations of diagnoses • Comorbidity calculated using the Charlson Comorbidity Index • National registry data, Swedish Prescribed Drug Registry national data (National Board of Health and Welfare): Medication with psychotropic drugs coded as N05A, N05B, N05C and N06A according to the ATC system
	(RQ3) How do patients experience the care provided at centers that implement PCBH?	• Interviews: Patient experiences with the behavioral consultant care they have received will be explored with interviews
Staff	(RQ4) How do health care staff members experience working with PCBH in terms of barriers to and facilitators for implementation?	• Interviews: Staff experiences of working with PCBH in terms of e.g., barriers and facilitators for implementation of PCBH in routine care
	(RQ5) How do mental health therapists’ experience their new PCBH-specific role as behavioral health consultants?	• Interviews: Mental health therapists’ experiences of taking on the new role as behavioral health consultants

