	(RQ6) How does implementation of the PCBH model affect the work environment?	Questionnaires • Sociodemographic factors: age, gender, profession, year in that profession, time employed at the primary health care center • Staff psychosocial factors: the COPSOQ III questionnaire • Staff work commitment: Utrecht Work Engagement Scale • Exhaustion among co workers: KEDS
Organization	(RQ7) How does PCBH influence accessibility to mental health care in primary care?	All based on local registry data: • Organization and context characteristics: number of employees, number of behavioral health consultants and physicians, number of listed patients, characteristics of the catchment area, care need index (CNI) and adjusted clinical groups • Number of visits to behavioral health consultants • Waiting times to first visit and revisits to behavioral health consultants and physicians • Types of mental health interventions (e.g. focused acceptance and commitment therapy, motivational interviewing, concise CBT, behavioral activation) • Format of delivery (e.g. internet-based or self-help materials) • Number of visits to physicians for patients diagnosed with F00-F99, Z56, Z73F, or prescribed medication with N05A, N05B, N05C and N06A
Economy	(RQ8) What is the cost-effectiveness of implementing and working based on PCBH?	The cost analysis will be based on several data sources, including registry data also used to address RQ1 and written documentation concerning the implementation activities undertaken during the implementation period for each participating primary care center

*Abbreviations: PCBH* Primary care behavioral health, *RQ* Research Question

Patient level:(RQ1) What are the effects of PCBH on patient outcomes compared to standard care?(RQ2) What characterizes patients who receive care according to the PCBH model compared to standard care?(RQ3) How do patients experience the care provided at centers that implement PCBH?

Staff level:(RQ4) How do health care staff members experience working with PCBH in terms of barriers to and facilitators of implementation?(RQ5) How do mental health therapists' experience their new PCBH-specific role as behavioral health consultants?(RQ6) How does implementation of the PCBH model affect the work environment?

Organization level:(RQ7) How does PCBH influence accessibility to mental health care in primary care?(RQ8) What is the cost-effectiveness of implementing and working based on PCBH?

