### Participants

#### Primary care center recruitment

Four pilot primary care centers have already been enrolled in the project, to test the protocol. After this pilot enrollment and adjustments of the implementation procedure, the protocol was adjusted to the final version. Following the pilot implementation of PCBH, a total of 24 primary care centers in RÖ will be enrolled in the research project (representing a total of 70% of all centers in this region). According to a staggered timetable, eight centers will be included in Year 1, eight in Year 2 and eight in Year 3, for a total of 24 centers over a three-year period. These 24 primary care centers in RÖ will be matched with 48 control centers from adjacent county councils in Jönköping, Kalmar and Örebro. Matching will be based on the number of listed patients, number of employees, number of behavioral health consultants and physicians and characteristics of the catchment area (CNI and ACG). A similar cluster-based approach has previously been used in research conducted at Linköping University [31].

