#### Statistical considerations

Quantitative data will be analyzed in both multilevel models and on separate levels: organization, staff and patients. Data will be collected from all centers who have initiated use of the PCBH model and in the initial analyses, all primary care centers will be considered intervention centers; i.e., analyses will be performed according to the intention to treat (ITT) principle. In addition, since features of the implementation might differ between centers, analyses will also be conducted based on centers with the highest fidelity to PCBH core components. Organization characteristics of the included primary care centers will also be collected and accounted for in the analyses, i.e., number of employees, number of behavioral health consultants and physicians, number of listed patients, characteristics of the catchment area, CNI and ACG. Furthermore, the PCBH model can be expected to require local adjustments for each primary care center. These adjustments will be carefully monitored for each participating center, and their impact on outcomes will be analyzed. In addition, data about mental health interventions (e.g., CBT) and the format of delivery (e.g., internet-based or self-help materials) will also be documented and addressed in the analyses.

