No human experiments will be conducted in this project. We estimate that there are minimal risks for participants (patients and staff) taking part in the project. Completing questionnaires regarding one’s health can be perceived as intrusive, and taking part in interviews can be perceived as uncomfortable. However, we believe that the benefits of this research outweigh the risks associated with participation. Indeed, mental health problems are a public health concern affecting a large proportion of the population both in Sweden and globally. This study has the potential to generate knowledge that is clinically relevant for primary care, benefiting a large proportion of the population suffering from mental health problems, thus contributing to the general good for the population and possibly providing better healthcare from a long-term perspective for the included patients. Regarding the included primary care staff, it is possible that psychosocial work environment problems will be identified, which offers the opportunity to improve the work environment for medical staff at both the intervention and control centers.

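### The RQ6 work-environment questionnaires are assigned to PCBH-centre staff only, which leaves no concurrent standard-care comparison on these scales and conflicts with the ethics text on control centres

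*Protocol article*

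**What the plan says.** All places are in the protocol article.

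- **Objectives.** The comparison is set up as "Twenty-four PCBH primary care centers will be compared with 48 standard care centers", and the next sentence adds "The results will be investigated at the patient, staff and organization levels". RQ6, a staff-level question, reads "How does implementation of the PCBH model affect the work environment".
- **Table 1, RQ6 row.** It lists the instruments (COPSOQ III, Utrecht Work Engagement Scale, KEDS) without saying which centres receive them.
- **RQ6: Work environment.** This section names the survey population: "Questionnaires will be administered to the staff at all PCBH centers regarding". It adds a second source, registry sick leave among primary care staff, with no restriction to PCBH centres.
- **Ethical considerations.** On the staff included in the project, it says that work-environment problems may be identified, "which offers the opportunity to improve the work environment for medical staff at both the intervention and control centers".
- **Primary care center recruitment.** The PCBH centres start in three waves: "eight centers will be included in Year 1, eight in Year 2 and eight in Year 3".
- **Statistical considerations.** "Data will be collected from all centers who have initiated use of the PCBH model".

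**The concern.** RQ6 is worded as a question about effect, and it is the only quantitative staff-level question; RQ4 and RQ5 are interview studies of experience. Whatever the project concludes about an effect on staff therefore rests largely on these scales.

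The survey population is stated rather than left out, and it excludes the standard-care centres. An analysis plan cannot repair that, because it cannot analyse staff who were never surveyed. The ethics section, however, reads as if control-centre staff supply work-environment data.

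Stress, engagement and exhaustion can change over three years for reasons unrelated to PCBH, such as workload and staffing. The article itself describes primary care as strained and under high work demands. Without unexposed staff measured at the same time, such change cannot be told apart from an effect of the model.

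**Working it through.** The article gives no figure for RQ6 that could be reproduced. The check is a comparison of the texts, a count from the timetable, and one line of algebra.

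**1. The texts side by side**

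| Section | Staff covered |
|---|---|
| RQ6: Work environment | PCBH centres only, for the questionnaires |
| Table 1, RQ6 | Not stated |
| Objectives | 24 PCBH and 48 standard-care centres; staff level named in a separate sentence |
| Ethical considerations | Intervention and control centres |

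The RQ6 and ethics sections do not agree. The Objectives do not contradict the RQ6 section outright, but a reader would expect staff outcomes to take part in the comparison announced there.

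**2. Who could act as a concurrent control**

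With waves of 8, the number of PCBH centres started by year y is 8y, and the number not yet started is 24 − 8y:

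| Year | Started | Not yet started | Standard-care centres named for the survey |
|---|---|---|---|
| 1 | 8 | 24 − 8 = 16 | 0 of 48 |
| 2 | 16 | 24 − 16 = 8 | 0 of 48 |
| 3 | 24 | 24 − 24 = 0 | 0 of 48 |

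A within-PCBH concurrent comparison is therefore possible in Years 1 and 2, provided that the waiting centres are surveyed then. Once all 24 have started, none is left in the stated survey population.

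**3. What the comparison identifies**

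Let the expected score at centre c on date t be a centre level a(c), plus a calendar effect b(t), plus θ if PCBH has started there.

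- Before-after at started centres only: [a + b(t2) + θ] − [a + b(t1)] = θ + [b(t2) − b(t1)]. The drift b(t2) − b(t1) enters in full. More respondents make the estimate more precise but do not remove the drift.
- The same difference minus that at centres not yet started, on the same two dates: θ + [b(t2) − b(t1)] − [b(t2) − b(t1)] = θ. The drift cancels if it is common to both groups of centres.

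Whether RQ6 can support an effect statement thus turns on shared survey dates across waves, or on surveying the control centres.

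**4. Whether those dates are fixed**

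The readable text gives no questionnaire dates. Fig. 1, which covers assessments, is not shown. The sentence on data from centres that have initiated PCBH raises doubt about surveys before the start. It cannot hold literally for all data, because the RQ1 section uses the year before implementation.

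**The case against.** The strongest reply is that survey timing is a detail that a condensed article may leave to the full protocol or analysis plan, or to Fig. 1. That is correct, and missing dates are not counted as an error here. The finding is the stated survey population and its conflict with the ethics section.

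A reader might go further and infer that RQ6 has no concurrent comparison at all, that it is an uncontrolled before-after study, or that the stepped design is not used for it. The document supports none of these. Its survey population covers all PCBH centres, which start in waves, so 16 and then 8 waiting centres could serve as controls. The article also describes a stepped-wedge design and multilevel models, with staff among the levels of analysis.

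Two further replies have weight:

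- RQ1 and RQ2 name standard care as the comparator and RQ6 does not; RQ3 to RQ5 draw on PCBH centres only. The 24 versus 48 comparison may therefore not have been meant for RQ6. This softens the tension with the Objectives but leaves the ethics text unexplained.
- Registry staff sick leave may cover control centres, so RQ6 as a whole is not shown to lack control data. Sick leave does not, however, measure stress, engagement or exhaustion.

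**Conclusion.** The point holds for the questionnaire outcomes of RQ6. As written, COPSOQ III, the Utrecht scale and KEDS go to none of the 48 standard-care centres. No concurrent standard-care comparison is available on them, and the ethics section conflicts with this.

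An effect reading is secure only if started and waiting waves are surveyed on the same dates, and only for the period in which some centres are still waiting. Otherwise secular drift cannot be separated from PCBH.

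No false-positive rate is given. It would need assumed values for drift, respondents per centre and intracluster correlation, together with a standard error that reflects repeated surveys of the same centres; the document supplies none of these. The algebra assumes additive calendar and centre effects, and drift common to all waves.

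Severity is minor to moderate: RQ6 is one of eight questions and the sample size is not based on it.

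**What to change.** 1. Make the RQ6 and ethics sections agree on whether control-centre staff are surveyed, and add the answer to the RQ6 row of Table 1. This costs a text edit.
2. If only PCBH centres are surveyed, give the questionnaire on common calendar dates in all 24 centres, beginning before the first wave starts. Analyse it as a stepped comparison with calendar-time effects and clustering by centre. The cost is some added respondent burden at centres already taking part; how much cannot be counted, because the number of planned rounds is not given. A round before a wave starts cannot be recovered afterwards, so this needs deciding early.
3. If neither control-centre surveys nor common dates are adopted, restate RQ6 as change in work environment at PCBH centres rather than an effect of PCBH. This costs only wording, but gives up the effect claim on these scales.

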##### RQ7: Accessibility of mental health care

Local registry data and document data from each included center will be used in terms of patient access to and utilization of healthcare, which are commonly reported outcomes in behavioral health research, typically with a wide variety of outcomes [33]. Several types of data will be collected: Organizational characteristics, including the number of employees, number of behavioral health consultants and physicians, number of listed patients, characteristics of the catchment area, CNI and ACG; number of visits and number of patients to behavioral health consultants; waiting times to first visit and revisits to behavioral health consultants and physicians; types of mental health interventions (e.g., focused acceptance and commitment therapy, motivational interviewing, concise CBT, behavioral activation); format of delivery (e.g., internet-based or self-help materials); and number of visits and number of patients to physicians for patients diagnosed with F00-F99, Z56, Z73F, or prescriptions of medication with ATC-codes N05A, N05B, N05C and N06A (also addresses RQ2).

##### RQ8: Cost-effectiveness of PCBH

Local registry data concerning sick leave, care accessibility, prescriptions, and health outcomes (also addressed in RQ1, RQ2 and RQ7), as well as the total cost of the implementation, collected by written documentation concerning the implementation activities undertaken during the implementation period for each of the included 24 primary care centers, will be used in the analysis of the cost-effectiveness of implementing and working according to the PCBH model. As both the costs and health outcomes of introducing the PCBH model are likely to extend beyond the 24-month study period, two analyses will be undertaken—a within-trial analysis based on data collected during follow-up as well as a long-term state-of-the-art decision-analytic model estimating expected long-term costs and health outcomes.

#### Statistical considerations

Quantitative data will be analyzed in both multilevel models and on separate levels: organization, staff and patients. Data will be collected from all centers who have initiated use of the PCBH model and in the initial analyses, all primary care centers will be considered intervention centers; i.e., analyses will be performed according to the intention to treat (ITT) principle. In addition, since features of the implementation might differ between centers, analyses will also be conducted based on centers with the highest fidelity to PCBH core components. Organization characteristics of the included primary care centers will also be collected and accounted for in the analyses, i.e., number of employees, number of behavioral health consultants and physicians, number of listed patients, characteristics of the catchment area, CNI and ACG. Furthermore, the PCBH model can be expected to require local adjustments for each primary care center. These adjustments will be carefully monitored for each participating center, and their impact on outcomes will be analyzed. In addition, data about mental health interventions (e.g., CBT) and the format of delivery (e.g., internet-based or self-help materials) will also be documented and addressed in the analyses.

#### Sample size

Approximately 3% of all patients in primary care receive an intervention by a behavioral health consultant [6, 13]. We hypothesize that this number will be at least 50% higher in the intervention group compared to the control group. A sample size based on a 50% increase, a power of 0.8 and a significance level of 0.05 yields a minimum of 1983 participants per group. Since we are using a design where heterogeneity of the populations and primary care centers probably will reduce the likelihood to detect meaningful changes, it is reasonable to double the number of participants to 3966 individuals per group. One of the pilot primary care centers has 14,841 listed patients. A study regarding Swedish primary care showed that approximately 66% of the population receives care annually at a primary care center [5]. It can thus be estimated that 9,795 (14,841 × 0.66) individual patients receive care annually at this center. If we assume that 3% [6, 13] of these patients receive a behavioral health consultant intervention, approximately 294 (9,795 × 0.03) patients annually receive a PCBH-based intervention. After the implementation of the PCBH delivery model, we estimate that this number will increase to 441 individual patients per year for one single primary care center (i.e., a 50% increase in the intervention group: 294 × 1,5 = 441). Since the project will involve 24 primary care centers, the requested sample size of at least 3966 individuals will not pose any difficulties, even considering that the number of listed patients among these centers ranges from approximately 4,500 to 21,500 listed patients (in December 2022). It should be noted that it is difficult to estimate the power of cluster studies because there can be heterogeneity within and between clusters.

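### The minimum of 1983 per group matches only an undeclared one-sided 5% test; at two-sided 0.05 it is 2518, so the twofold heterogeneity allowance is about 1.58

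*Protocol article*

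**What the plan says.** The Sample size section of the protocol article builds its target from four inputs.

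- Control rate: "Approximately 3% of all patients in primary care receive an intervention by a behavioral health consultant".
- Effect: "We hypothesize that this number will be at least 50% higher in the intervention group compared to the control group", which takes 3% to 4.5%.
- Power and level: "a power of 0.8 and a significance level of 0.05 yields a minimum of 1983 participants per group".
- Allowance for heterogeneity of populations and centers: "it is reasonable to double the number of participants to 3966 individuals per group".

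The level is given only as "a significance level of 0.05". Neither this section nor Statistical considerations nor Analysis of quantitative data says whether tests are one-sided or two-sided.

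**The concern.** The article prints a specific number and says that its stated inputs produce it. A reader who repeats the calculation at the usual two-sided 0.05 does not get 1983. Either the figure is too small for the test that most readers will assume, or a one-sided level was used without saying so.

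The number matters because it is the base for the doubling, and the doubling is the only numerical allowance the article makes for differences between populations and centers. If the base is too low, part of the doubling is spent on making up the significance level and less is left for heterogeneity. The same section concedes that power in cluster studies is hard to estimate, so the size of that margin should be reported correctly.

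**Working it through.** **Inputs** (all from Sample size): p1 = 0.03; p2 = 0.03 × 1.5 = 0.045; difference d = 0.015; mean rate p̄ = 0.0375; power 0.80 (z = 0.8416); level 0.05; equal groups, since the figure is given per group. No dropout is applied.

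**Formula** (pooled two-proportion, no continuity correction):

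n = [z_α·√(2p̄(1−p̄)) + z_β·√(p1(1−p1) + p2(1−p2))]² / d²

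- √(2 × 0.0375 × 0.9625) = √0.0721875 = 0.26868
- √(0.0291 + 0.042975) = √0.072075 = 0.26847

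**Step 1: reproduce the plan's figure.** With one-sided 5%, z_α = 1.6449:

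n = (1.6449 × 0.26868 + 0.8416 × 0.26847)² / 0.000225 = (0.44193 + 0.22595)² / 0.000225 = 1982.5, rounded up to **1983**. The match is exact.

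**Step 2: two-sided 5%.** With z_α = 1.9600:

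n = (0.52660 + 0.22595)² / 0.000225 = 2517.003, rounded up to **2518**. The ratio 2518/1983 is 1.27.

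**Step 3: could another two-sided method give 1983?** Equal groups, per group:

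| Method | One-sided 0.05 | Two-sided 0.05 |
|---|---|---|
| Pooled | 1983 | 2518 |
| Unpooled | 1981 | 2515 |
| Arcsine | 1965 | 2494 |
| Log odds ratio | 2010 | 2552 |
| Log risk ratio | 2015 | 2557 |
| Continuity-corrected | 2114 | 2649 |

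The standard two-sided methods run from 2494 to 2649. A crude version that applies the control-rate variance to both groups gives 2031 two-sided, which is nearer but is neither standard nor equal to 1983. Allocation of 1:2, following the 24 and 48 centers, gives 1838 intervention and 3676 control patients two-sided (pooled), which is not 1983 either.

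**Step 4: power.** Power = Φ[(d√n − z_α × 0.26868) / 0.26847].

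| n per group | One-sided 0.05 | Two-sided 0.05 |
|---|---|---|
| 1983 | 80.0% | 70.1% |
| 3966 | 96.9% | 94.0% |

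These values ignore clustering.

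**Step 5: what the doubling buys.**

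- Against the one-sided minimum: 3966/1983 = 2.00.
- Against the two-sided minimum: 3966/2518 = 1.58.
- Doubling the two-sided minimum: 2 × 2518 = 5036.

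So on a two-sided reading, 3966 per group keeps 80% power only while the variance inflation stays below about 1.58.

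**The case against.** Four points can be made on the other side.

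**One-sided testing may have been intended.** The hypothesis is worded in one direction, and the logic model lists its intended outcomes as improvements. If the test is one-sided, 1983 is correct and the only fault is that the reader is not told. This stands, and it makes the 70.1% conditional. A reader might infer that the article commits itself to two-sided tests because its research questions on patient outcomes and accessibility are neutrally worded, or because it speaks of showing effectiveness or its absence. The first leans that way but fixes no test. The second appears in the Abstract and at the end of the Discussion, not in the research questions, and it sets effect against no effect, which a one-sided test also addresses.

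**The trial is not run at 1983.** A reader might infer from the 70.1% that the trial is underpowered. The article does not support that, because its requested sample is 3966 per group, which is above 2518. With the planned 1:2 ratio of centers, even 1983 intervention and 3966 control patients would have about 83% two-sided power before clustering.

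**Patient numbers are not the limit.** Registry data are taken from all eligible patients. If all 24 intervention centers had the smallest list size quoted, 4,500 × 0.66 × 24 = 71,280 patients would be seen each year, about 14 times 5036. This stands, and it is why the point is confined to reporting.

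**The factor of 2 is a judgement.** It is not derived from a design effect, so a move from 2 to 1.58 need not alter the design. That is fair, but the article still presents the factor as its safeguard, and its size is misstated if testing is two-sided.

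**Conclusion.** The point holds in a conditional form. The stated inputs give "a minimum of 1983 participants per group" only with a one-sided 5% level, which the article does not declare. At the conventional two-sided 0.05 the minimum is 2518, and 1983 has 70.1% power instead of the stated 80%. As written, the figure and the level do not fit together for a reader who takes 0.05 in its usual sense.

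The consequence is limited. The operative 3966 exceeds the two-sided minimum, so what is overstated is the heterogeneity allowance: about 1.58, not 2. The article gives no between-center variance, so these figures cannot show whether 1.58 or 2 would be enough.

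The numbers rest on equal groups, the pooled formula without continuity correction, rates of 3% and 4.5%, and no dropout.

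**What to change.** State in the Sample size section whether the 0.05 level is one-sided or two-sided, and use the same convention in Analysis of quantitative data.

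- **If two-sided:** replace 1983 with 2518 per group. Then either replace 3966 with 5036, if the factor of 2 is kept, or keep 3966 and describe it as a 1.58-fold allowance over the minimum.
- **If one-sided was intended:** say so explicitly beside 1983. The figures 1983 and 3966 can then stay.

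The cost is a few words of text. No extra recruitment, data collection or change of design is needed.

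### The sample size of 3,966 per group is a doubled individual-level figure for consultant reach; it does not establish power of 0.8 for the comparison of 24 with 48 centres

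*Protocol article*

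**What the plan says.** All of the calculation is in the protocol article, Sample size.

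- Control proportion: "Approximately 3% of all patients in primary care receive an intervention by a behavioral health consultant".
- Effect: "We hypothesize that this number will be at least 50% higher in the intervention group compared to the control group".
- Base figure: "a power of 0.8 and a significance level of 0.05 yields a minimum of 1983 participants per group". The section does not say whether the test is one- or two-sided.
- Allowance for heterogeneity of populations and centres: "it is reasonable to double the number of participants to 3966 individuals per group".
- Feasibility, worked for one pilot centre: "It can thus be estimated that 9,795 (14,841 × 0.66) individual patients receive care annually at this center". Of these, "approximately 294 (9,795 × 0.03) patients annually receive a PCBH-based intervention", projected to rise to 441 after implementation.
- Conclusion: "Since the project will involve 24 primary care centers, the requested sample size of at least 3966 individuals will not pose any difficulties".

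The section closes by conceding that power is hard to estimate in cluster studies.

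Elsewhere, Study setting gives 24 intervention and 48 control centres. Primary care center recruitment gives three yearly steps of eight centres. Analysis of quantitative data foresees multilevel models. Table 1 under Objectives assigns two outcomes to RQ1: sick leave due to mental health problems, and "Referrals to secondary psychiatric care based on electronic medical records". Visits to and patients of behavioral health consultants are listed under RQ7.

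**The concern.** Three features of the printed calculation do not fit the trial.

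1. **Clustering.** The base formula treats patients as independent and the groups as equal in size. The doubling is the only allowance for clustering, and it is not derived from between-centre variation, the number of centres, the 1:2 ratio or the steps. When whole centres enter from registries, precision depends mainly on how many centres there are and how much they differ.
2. **Units.** The 3,966 are people of whom 3% or 4.5% see a consultant, so they are attenders. The feasibility check counts people who did see a consultant.
3. **Outcome.** The quantity sized is reach of consultant care. RQ1 concerns sick leave and referrals among patients identified by diagnosis or psychotropic prescription (Patient recruitment), and the calculation does not bear on those.

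At stake is how the results are read. A reader may take the comfortable headcount as evidence that the centre comparison has power of 0.8, or carry that figure over to the RQ1 outcomes.

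**Working it through.** **Inputs from the protocol article.** p1 = 0.03; p2 = 0.03 × 1.5 = 0.045; difference 0.015; power 0.8; alpha 0.05; 24 and 48 centres; 9,795 attenders per year at the example centre; smallest centre about 4,500 listed patients, hence 4,500 × 0.66 = 2,970 attenders. The documents give no ICC or between-centre CV, so the CV values below are assumptions.

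**Step 1: reproduce 1,983.** Two-proportion formula with pooled variance, independent patients, 1:1:

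n = [z_α √(2 p̄(1 − p̄)) + z_β √(p1(1 − p1) + p2(1 − p2))]² / (p2 − p1)²

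with p̄ = 0.0375, 2 p̄(1 − p̄) = 0.0721875, p1(1 − p1) + p2(1 − p2) = 0.072075 and z_β = 0.842.

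- One-sided, z_α = 1.645: n = 1,982.5, rounded up to **1,983**, an exact match.
- Two-sided, z_α = 1.960: n = 2,517.003, rounded up to **2,518**.

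Other two-sided variants give 2,494 (arcsine), 2,515 (unpooled) and 2,649 (continuity-corrected); none gives 1,983. With 1,983 per group a two-sided test has power of about 0.70 even without clustering.

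**Step 2: the doubling.** 2 × 1,983 = 3,966. Against the two-sided base the margin is 3,966 / 2,518 = 1.58, not 2.

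**Step 3: units.** Among 3,966 attenders the expected consultant recipients are 3,966 × 0.03 = 119 to 3,966 × 0.045 = 178. The protocol compares 3,966 with recipients: 24 × 441 = 10,584. The matching count is attenders: 24 × 9,795 = 235,080, or 24 × 2,970 = 71,280 if every centre were the smallest. Headcount is ample either way. The example centre alone, with 9,795 attenders, exceeds 3,966, so reaching that number says nothing about whether there are enough centres.

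**Step 4: what governs power for 24 versus 48 centres.** This is a simplified illustration: post-period only, unadjusted, two-sided, m attenders per centre, between-centre SDs s1 (control) and s2 (intervention):

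SE² = [p2(1 − p2)/m + s2²]/24 + [p1(1 − p1)/m + s1²]/48; power = Φ(0.015/SE − 1.96).

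Two assumptions about the SDs are shown: the same CV k in both arms (s1 = 0.03k, s2 = 0.045k), and equal SD in both arms (s1 = s2 = 0.03k).

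| CV k (assumed) | Same CV, m = 9,795 | Same CV, m = 2,970 | Equal SD, m = 9,795 |
|---|---|---|---|
| 0.5 | 84% | 83% | 98% |
| 0.6 | 69% | 68% | 91% |
| 0.8 | 45% | 45% | 70% |

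Example, k = 0.6, same CV, m = 9,795. The sampling terms are 0.0000044 and 0.0000030; the between-centre terms are 0.000729 and 0.000324. SE = 0.00611, 0.015/SE = 2.454, and power = Φ(0.494) = 69%. With equal SD, SE = 0.00453, 0.015/SE = 3.313 and power = Φ(1.353) = 91%.

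More than tripling the attenders per centre moves power by about one percentage point at most. The between-centre assumption moves it by tens of points.

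**The case against.** **The section carries its own caveat.** It says that cluster power is hard to estimate, and its assurance concerns reaching 3,966 people, not securing 80% power in the cluster comparison. This stands, and it limits the criticism. The caveat does not repair the printed figure, which remains the only basis offered for the size of the trial.

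**The trial may well be adequately powered.** A reader might infer from Step 4 that it is underpowered. The documents do not support that. The CV is unknown, and the illustration leaves out matching, covariate adjustment, the baseline year and the staggered entry. The lower figures also depend on giving both arms the same CV, which makes the intervention arm's SD 1.5 times as large; with equal SD, 69% becomes 91%.

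**The doubling cannot be read as one hidden ICC.** Spreading 3,966 over 24 centres (165 each), a design effect of 2 would imply an ICC of 1/164.25 = 0.006, which might look too small. But whole centres enter the data. With 9,795 attenders in each of 24 centres the available design effect is 235,080 / 1,983 = 118.5, or an ICC of about 117.5 / 9,794 = 0.012 (0.009 against 2,518). So the doubling is not shown to be too small; it has no stated basis.

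**The unit slip is harmless for headcount.** Correct: recipients are a subset of attenders, so 10,584 recipients guarantee more than 3,966 attenders. Too few patients should not be inferred.

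**No power is claimed for RQ1.** Also correct. The section says what it sizes, the article names no primary outcome, and further power calculations may sit in a fuller document. What remains is that the one printed calculation should say which research question it serves.

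**Conclusion.** The point holds as a defect in the justification of the sample size. The multiplications are all right; the calculation does not describe the planned comparison.

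- The base figure needs an unstated one-sided 0.05 test; a two-sided test raises it from 1,983 to about 2,518.
- The doubling contains none of the quantities that determine precision with 24 and 48 centres.
- The feasibility check mixes denominator and numerator. This does no harm to headcount, but meeting 3,966 is not evidence of power of 0.8.
- The result applies to consultant reach (RQ7) and says nothing about sick leave or referrals.

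Power for reach is therefore not established, and it is not shown to be inadequate. Over assumed CVs of 0.5 to 0.8 the illustration runs from 84% down to 45% with the same CV in both arms, and from 98% down to 70% with equal SD. These ranges rest on a simplified post-period model and on CVs that the documents do not give.

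**What to change.** Revise the Sample size section as follows.

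1. State the sidedness and correct the base figure: about 2,518 per group if two-sided, or 1,983 declared as one-sided.
2. Replace the doubling by power for 24 versus 48 centres over a stated ICC or between-centre CV range, saying how the between-centre SD is assumed to behave in each arm and taking the baseline year into account. Check the range against pre-implementation registry data from the centres when these are available.
3. Replace the comparison of 441 recipients per centre with 3,966 by attender counts for both groups.
4. State that the power of 0.8 refers only to reach of consultant care (RQ7) and not to the RQ1 outcomes.

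The cost is a recalculation and a reworded paragraph; no centres are added. Checking the range has to wait for registry data from the participating centres. The downside is that the stated power may become less favourable than 0.8.
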